## Abstract

**Background:**

ST-segment elevation myocardial infarction (STEMI) still causes significant mortality and morbidity despite best-practice revascularization and adjunct medical strategies. Within the STEMI population, there is a spectrum of higher and lower risk patients with respect to major adverse cardiovascular and cerebral events (MACCE) or re-hospitalization due to heart failure. Myocardial and systemic metabolic disorders modulate patient risk in STEMI. Systematic cardiocirculatory and metabolic phenotyping to assess the bidirectional interaction of cardiac and systemic metabolism in myocardial ischemia is lacking.

**Methods:**

Systemic organ communication in STEMI (SYSTEMI) is an all-comer open-end prospective study in STEMI patients > 18 years of age to assess the interaction of cardiac and systemic metabolism in STEMI by systematically collecting data on a regional and systemic level. Primary endpoint will be myocardial function, left ventricular remodelling, myocardial texture and coronary patency at 6 month after STEMI. Secondary endpoint will be all-cause death, MACCE, and re-hospitalisation due to heart failure or revascularisation assessed 12 month after STEMI. The objective of SYSTEMI is to identify metabolic systemic and myocardial master switches that determine primary and secondary endpoints. In SYSTEMI 150–200 patients are expected to be recruited per year. Patient data will be collected at the index event, within 24 h, 5 days as well as 6 and 12 months after STEMI. Data acquisition will be performed in multilayer approaches. Myocardial function will be assessed by using serial cardiac imaging with cineventriculography, echocardiography and cardiovascular magnetic resonance. Myocardial metabolism will be analysed by multi-nuclei magnetic resonance spectroscopy. Systemic metabolism will be approached by serial liquid biopsies and analysed with respect to glucose and lipid metabolism as well as oxygen transport. In summary, SYSTEMI enables a comprehensive data analysis on the levels of organ structure and function alongside hemodynamic, genomic and transcriptomic information to assess cardiac and systemic metabolism.

**Discussion:**

SYSTEMI aims to identify novel metabolic patterns and master-switches in the interaction of cardiac and systemic metabolism to improve diagnostic and therapeutic algorithms in myocardial ischemia for patient-risk assessment and tailored therapy.

**Trial registration:**

Trial Registration Number: NCT03539133

**Supplementary Information:**

The online version contains supplementary material available at 10.1186/s12872-023-03210-1.

## Background

ST-segment elevation myocardial infarction (STEMI) continues to confer a substantial burden of morbidity and mortality with plateauing numbers since 2008 [1, 2]. Latecomer STEMI patients, increased patient age and the associated multimorbidity, and STEMI complicated by cardiogenic shock (CS) counterbalance the improvements in prehospital care, ambulance logistics, pharmacotherapy and timely primary percutaneous coronary intervention (pPCI) [2, 3]. Coronary vessel occlusion by plaque erosion and microembolization have become increasingly frequent compared to plaque rupture, which in turn leads to specific types of myocardial ischemia and infarction [4, 5]. At present, almost one-half of patients still demonstrate left ventricular (LV) postinfarct remodeling [6]. Although there is no difference in long-term survival between remodelers and non-remodelers, LV remodelers experience a higher rate of hospitalization for heart failure [6]. This formulates the need to intensify stratification and therapeutic strategies starting in the acute phase of myocardial ischemia [7]. In elderly STEMI patients, metabolic comorbidities such as type 2 diabetes mellitus (T2DM), anemia, and chronic kidney disease (CKD) become increasingly prevalent. Persons with T2DM exhibit a higher incidence of STEMI and an increased mortality risk [8, 9]. When anemia is added to CKD and T2DM, the prognosis further deteriorates [10]. Of note, T2DM is associated with impaired mitochondrial efficacy not only in skeletal muscle [11] but also in cardiomyocytes [12]. Recently, endotypes (subtypes, clusters) of T2DM with distinct metabolic and inflammatory features have been shown to have adverse cardiovascular risk profiles, particularly among patients with a higher degree of insulin resistance [13, 14]. In parallel, the proportion of STEMI patients without standard modifiable cardiovascular risk factors (SMuRFs) has steadily increased from 14 to 27% in the last decade, particularly among younger individuals, with an almost 50% higher 30-day mortality rate than patients with SMuRFs [15]. This highlights the unmet need to identify unknown confounders in the interactions of systemic and cardiac metabolism. In this regard, systematic cardiocirculatory and metabolic phenotyping to assess the bidirectional interaction of cardiac and systemic metabolism in STEMI and during cardiac healing is lacking.

The **objective** of the present cohort study (systemic organ communication in STEMI, SYSTEMI) is to identify metabolic systemic and myocardial master switches that determine outcomes after STEMI. The aims are as follows: **(i)** to characterize myocardial and systemic metabolism in STEMI together with early regional LV function, LV remodeling, myocardial texture and infarct characteristics at index hospitalization **(ii)** to characterize the interaction of systemic and myocardial master switches using unsupervised cluster analysis to identify patients with a specific metabolic risk phenotype at index hospitalization **(iii)** to identify novel therapeutic master switches and networks prone to interventions and modulations.

## Methods/Design

### Design, setting and endpoints of the study

SYSTEMI is an investigator-initiated, open-end prospective, observational, multicentric, cohort study of all-comer patients with STEMI supported by the German Research Council (CRC 1116, Grant No. 236,177,352). Ethics approval was given by the local ethics committees (Heinrich-Heine-University, Düsseldorf, Germany; and Landesärztekammer Nordrhein) complying with the Declaration of Helsinki under reference numbers 5961R and 2,021,055. SYSTEMI is registered at www.clinicaltrials.gov: NCT03539133. SYSTEMI will recruit patients at the academic main-hospital of Heinrich Heine University Düsseldorf, Germany with > 150 STEMI per year, as well as in secondary pPCI -centres within the academic network of Heinrich Heine University Düsseldorf (“Heart-net”), Germany with > 80 STEMI per year. To optimize recruitment efficacy, training sessions have been performed with the interventional staff on call and the study nurses to best inform the patients about the study dependent examinations during their guideline directed diagnostics and therapy at index hospitalisation. As shown in the study flow (Fig. 1A), data will be collected at the index hospitalization (index event within the catheter laboratory + 1–5 days), as well as at follow-up (FU) visits at 6 and 12 months after STEMI at each of the recruiting centers. Follow up phone calls will be performed annually for up to five years. As shown in Fig. 1B, the primary endpoints are imaging-derived LV ejection fraction (LVEF), indexed LV stoke volume (SVi), increase in LV indexed end-diastolic volume (LVEDVi) and LV texture (T1, T2, ECV) using either 3-dimensional echocardiography or CMR 6 months after STEMI as well as angiography derived coronary patency rate at 6 month after STEMI. Secondary endpoint is a composite of all cause mortality, MACCEs (cardiovascular death, nonfatal stroke or myocardial infarction) and rehospitalization due to heart failure within 12 months after STEMI.

**Fig. 1 Fig1:**
[figure not shown]
SYSTEMI, systemic organ communication in STEMI, was designed to identify novel metabolic systemic and cardiac masterswitches and networks that determine primary and secondary endpoints, ultimately to improve STEMI care in patient with concomitant metabolic disorders A) Study Flow Chart of SYSTEMI. Patients with STEMI > 18 years of age will be screened and enrolled for study participation if exclusion criteria are not met. Patients fulfilling exclusion criteria are documented within a separate registry. During index hospitalisation 6 Visits (Δ) will be conducted for assessment of myocardial and systemic master switches. At 6 month visit 7 will take place for assessment of the primary endpoints. At 12 month secondary endpoint assessment will be conducted via telephone call while further observation will be conducted yearly. B) Definition of master switches and endpoints. STEMI = ST-segment elevation myocardial infarction, EF = Ejection fraction, SVi = Stroke volume index, WT = Wall thickening, T1 = T1-relaxation time, T2 = T2-relaxation time, ECV = Extracellular volume fraction, Cr = Creatinine, ATP = Adenosine triphosphate, IFG = Impaired Fasting Glucose, IGT = Impaired Glucose tolerance, T2DM = Type 2 Diabetes Mellitus, FA = Fatty acids,

### Characteristics of participants

According to our all-comer design, all patients referred to our hospital with a STEMI diagnosis will be asked for informed consent, if no exclusion criterion is present. The main exclusion criteria are age < 18 years, living abroad, and a life-limiting disease with a life expectancy of < 1 year or an unfavourable neurologic outcome. Patients who meet the exclusion criteria will be enrolled in a parallel STEMI register.

Patient selection and short informed consenting will be done by the physician on call at the coronary care unit immediately before the start of pPCI. Before the final consent is given, the investigator or his/her representative will explain verbally the aim, method, source of funding, and the anticipated benefits and potential risks to the participants and answer all questions regarding the study. As part of the general informed consent, all screening subjects are being asked for serial collection of blood samples and its storage in a biobank as well as further genetic analysis. Biosamle processing and storage is done according to existing standard operating procedures (SOPs) at -80 °C. Biosample access is regulated by the SOPs and granted by standardized evaluation upon formal request. Apart from liquid specimen, electronic patient data are collected systematically and online within the Duesseldof Outcome, Safety and Risk Assessment Registry (DOSAR) via health level (HL)-7 interfaces connected to clinical data systems. All requirements of the General Data Protection Regulation are met. A unique participant number will be allocated to each participant (pseudonymization) and assigned chronologically prior to proceeding with study screening. The sequential identification numbers will be used to collect, store, and report participant information.

### Study processes and protocols

The detailed study protocol is given in SPIRIT Table 1. The treatment of STEMI patient will be conducted according to current guidelines [16]. For assessing initial effects of STEMI on the heart and circulation, we will conduct biplane cineventriculography (CVG) as well as right heart catheterisation during pPCI (V0). This will provide information on LV function and circulatory regulation before reperfusion. During right heart catheterization we will measure cardiac output according to the fick`s law, systemic vascular and pulmonary vascular resistance and AVDO_2_ for oxygen consumption. In parallel, the first liquid biopsies will be generated. The liquid biopsies will serve for assessing basic laboratory parameters including lactate to assess cardiogenic shock and biobanking specimen aiming at subsequent cellular, biochemical, immunological and genetic analyses. Guideline directed repetitive ECG recordings and monitoring will be conducted (V1).

**Table 1 Tab1:** SPIRIT (Standard Protocol Items: Recommendations for Interventional Trials) figure showing important events and their respective time points during the study period in the cohort study

Action	Study Periode											
	Enrolment	Observation										
		Index Hospitalisation						FU Hospitali-sation	FU Call			
Visit (V) / Phone Call (PC)	Screening	V1	V2	V3	V4	V5	V6	V7	PC8	PC9	PC10	P111
Time Point (d)	0	0	1	2	3	4	5	180	365	730	1095	1460
*Enrolment*												
Eligability Screen	X											
Informed Consent	X											
Pseudonymisation	X											
*Assessments*												
Mail-Reporting (internal)		X	X	X	X	X	X	X				
Questionnaires & PE			X	X	X	X	X	X				
CA		X						X				
LHC/RHC		X						X				
CVG		X						X				
TTE			X		X			X				
CMR			X		X			X				
CMR + MRS							X	X				
Tonometry							X	X				
FMD							X	X				
4D Flow CMR							X	X				
12-lead ECG		X	X	X			X	X				
Monitoring		X	X	X								
Blood Sampling & Biobanking		X	X				X	X				
OGTT							X	X				
*Outcome Assessment*												
Endpoints								P	S	O	O	O

PE = Patient Empowerment, CA = Coronary Angiography, LHC = Left Heart Catheterisation, RHC = Right Heart atheterisation, CVG = Cineventriculography, TTE = Transthoracic echocardiography, CMR = Cardiovascular Magnetic Resonance, MRS = Magnetic Resonance spectroscopy, FMD = Flow Mediated Dillatation, ECG = Electrocardiogram, OGTT = oral glucose tolerance test, P = Primary Endpoint, S = Secondary Endpoint, O = Observational

Within the first and third day after reperfusion we will conduct additional cardiac imaging with transthoracic echocardiography and in a subset of patients cardiovascular magnetic resonance (CMR) (1.5 & 3.0T Achieva, PHILIPS Healthcare, Best, Netherlands) including measurements of ventricular mass, volume, function and myocardial relaxometry (V2 + V4). Cine imaging will be used to calculate pressure-volume curves by taking phase-to-phase volumes of short-axis slices, blood pressure and left ventricular end-diastolic pressure measurements from acute catheterization measurements [17]. Additionally, native relaxometric mapping of the myocardium (T1, T2, T2*) [18], gadolinium contrast-enhanced imaging and postcontrast relaxometric mapping (T1, extracellular volume fraction, ECV) will be performed to assess the myocardial inflammation/edema extent, extracellular volume, fibrosis and iron content. For this, validated sequences will be used as outlined in Additional File Table 1. Gadolinium-enhanced images will be used to assess markers of infarcted tissue, such as edema, infarct size (IS), microvascular obstruction (MVO), and intramyocardial hemorrhage (IMH). Certified CMR evaluation software will be used for all analyses (CVI42, Circle Cardiovascular Imaging Inc., Calgary, Alberta, Canada or Sectra Workstation IDS7, Version 19.3.6.3510). This will be accompanied by an additional liquid biopsy. These early measurements after reperfusion will give insight in very early adaptations in ventricular volume and dimensions, which will serve to associate ventricular volume and dimension with systemic blood derived markers. Blood samples will also be collected to assess arterial or venous lactate, hemoglobin A1c (HbA1c), fasting blood glucose and insulin for calculating the Homeostasis Model Assessment indices (HOMA-IR and HOMA-B). Additionally, a detailed assessment of anemia will be performed, including parameters of RBC turnover, formation, (dys)function, and hemolysis. Specifically, we will address absolute and relative iron deficiency (ID), one of the most common reasons of anemia, especially in elderly patients with comorbidities, by measuring free iron, ferritin, transferrin, the soluble transferrin receptor and transferrin saturation in the collected blood samples. This will be done during V2.

During V2-V5 we will additionally empower the patients to stick to the study by providing detailed information about his health status and study specific examination results. Five days after pPCI (V6), we will again apply echocardiography and CMR with the addition of magnetic resonance spectroscopy (MRS). For regional myocardial metabolic profiling, ^1^ H and ^31^P-MRS, which are key techniques for measuring fatty acids (FA) and total creatine as well as ATP, Pi and pH, will be integrated into the clinical CMR protocol 5 days and 6 months after STEMI. For ^1^ H-MRS, navigator-free metabolite-cycled spectroscopy using a voxel size of approximately 4–6 ml (10 × 15 × 35 mm3) and ≈ 144 averages (7:50 min) will be applied [19]. jMRUI/AMARES will also be used to analyze ^31^P spectra. Reconstruction will be performed using a customized reconstruction pipeline in ReconFrame (GyroTools LLC, Zürich, Switzerland). jMRUI/AMARES will also be used to analyze MR spectra. Simultaneously, we will have information through liquid biopsies on the diabetes endotype in patients with overt diabetes and on glucose tolerance in patients without diabetes by applying oral glucose tolerance test (OGTT). To asses circulatory adaptations of large conductive arteries, we will apply pulse wave velocity measurements by 4-dimensional velocity-encoding in CMR and by carotid-femoral applanation tonometry using Sphygmocor® technology (AtCor Medical, West Ryde, Australia). The central aortic blood pressure, pulse pressure (PP) and augmentation index (AIX) will be assessed. To assess the primary endpoints, that is LV function, LV remodeling, LV metabolism, LV texture and coronary patency, after complete myocardial healing at 6 months after STEMI, we scheduled further examinations (V7). These examinations comprise of a coronary angiography, echocardiography, CMR, OGTT, applanation tonometry and additional liquid biopsies. The secondary endpoints will be assessed by a telephone call at 12 months (PC8). Further observational phone calls (PC9-11) are planned on a yearly basis.

### Study organisation and leadership

The SYSTEMI Steering Committee is responsible for the scientific content of the protocol, oversees the study steps, and checks adherence to “Good Clinical Practice” and the study protocol as well as performance. Study conduction will follow the SOP of the Clinical Trial Unit (CTU) of the University Hospital of Düsseldorf. The SYSTEMI Endpoint Adjudication Committee (EAC) will adjudicate clinical endpoints based on data provided by the clinical trial sites. This procedure will be supervised by the trial coordination center (TCC, Koordinierungszentrum für Klinische Studien, KKS) at Heinrich Heine University. The trial management committee (TMC) meets once a week and the steering committee twice a year to review trial conduct. The data monitoring committee (DMC) consist of a data manager and participants of the external advisory board. Patient data are collected systematically and online within the DOSAR Registry via health level (HL)-7 interfaces connected to clinical data systems. All requirements of the General Data Protection Regulation are met. The DMC will report in a weekly manner organizational aspects of data collection and handling as well as quality and completeness reports. Data quality and completeness is of prime importance in SYSTEMI. Regular audits are conducted synchronized to the annual meeting of the Cardiovascular Research Institute Düsseldorf (CARID). Upon formal request according to our internal SOP, access to primary data can be given. This process is guided by the SYSTEMI Steering Committee, which is responsible for the scientific content of the study data.

### Statistical approach

SYSTEMI was designed as open-end prospective cohort study in all comer STEMI patients. No formal sample size calculation has been performed. It was anticipated that more than 160 STEMI patients per year will be a realistic recruitment speed on the basis of expected STEMI patients at host institutions to reach a total sample size of > 1000 STEMI patients.

This cohort study was designed to unravel novel master switches and markers of metabolic networks in STEMI patients to further facilitate risk stratification and identify novel therapeutic targets in STEMI. For primary endpoints, logistic regression analysis will be used to model the predefined outcome data with impact of covariates. The effects of the independent parameters in these regression models will be estimated (odds ratio, hazard ratio) and presented with 95% confidence intervals. Network analysis using machine learning approaches for unsupervised metabolic cluster identification will be conducted. Secondary endpoint analysis will be performed using Kaplan–Meier plots and the log-rank test. Two-tailed p values below 0.05 will be considered indicative of statistically significant differences. Since significant interactions of master switches within the metabolic network are anticipated, interim analysis will be done after 500 and 1000 patients for a robust statistical power calculation and re-adjustment of investigations.

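### Logistic regression is assigned to all primary endpoints, although the imaging endpoints are continuous, and it cannot yield the hazard ratio the plan promises

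*Protocol article*

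**What the plan says.** In the protocol article, the section on design, setting and endpoints lists the primary endpoints. The list opens with "the primary endpoints are imaging-derived LV ejection fraction (LVEF), indexed LV stoke volume (SVi), increase in LV indexed end-diastolic volume (LVEDVi"), continues with "LV texture (T1, T2, ECV) using either 3-dimensional echocardiography or CMR 6 months after STEMI", and closes with "angiography derived coronary patency rate at 6 month after STEMI". None of the imaging measures is defined there by a threshold or as a responder outcome. The section on study processes also counts LV metabolism among the primary endpoints, and this too is measured on a continuous scale. The legend of Fig. 1 fixes the timing: "At 6 month visit 7 will take place for assessment of the primary endpoints".

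The Statistical approach section then names one model for the whole set: "For primary endpoints, logistic regression analysis will be used to model the predefined outcome data with impact of covariates". The next sentence reads: "The effects of the independent parameters in these regression models will be estimated (odds ratio, hazard ratio) and presented with 95% confidence intervals". For the secondary endpoint the plan is: "Secondary endpoint analysis will be performed using Kaplan–Meier plots and the log-rank test". The article names no linear model and no Cox or other hazard model.

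**The concern.** The scale of the endpoints, the model and the effect measures do not fit together.

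- **Model.** In its ordinary form, logistic regression takes a binary outcome. It suits patency. LVEF, SVi, LVEDVi increase, T1, T2 and ECV would each have to be reduced to a yes/no variable first. That discards information and obscures any graded relation between a metabolic marker and the outcome, which is what the study sets out to find.
- **Effect measure.** A hazard ratio describes a rate of events over time. The primary endpoints are read at one fixed visit and have no event time, and a logistic model estimates odds ratios only. As written, one of the two promised effect measures has no model behind it.

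**Working it through.** **1. Endpoint by endpoint**

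| Primary endpoint | Scale as defined | Logistic regression without a cut? |
|---|---|---|
| LVEF, SVi | continuous, 6 months | no |
| Increase in LVEDVi | continuous change | no |
| T1, T2, ECV | continuous, 6 months | no |
| Coronary patency | open or not | yes |

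Six of the seven measures in the design section do not suit the assigned model. LV metabolism, listed in the study-processes section, would be a further continuous one.

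**2. Information lost by cutting**

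The article states that no formal sample size calculation was done, so there is no figure to reproduce. For a normal outcome and a small effect, the efficiency of a logistic analysis with a proportion p beyond the cut, relative to a linear model, is

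E = φ(z_p)² / [p(1 − p)].

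| p | E | 1000 × E | 1/E |
|---|---|---|---|
| 0.50 | 0.637 | 637 | 1.57 |
| 0.30 | 0.576 | 576 | 1.74 |
| 0.20 | 0.490 | 490 | 2.04 |
| 0.10 | 0.342 | 342 | 2.92 |

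For p = 0.50: φ(0) = 0.3989, and 0.3989²/0.25 = 0.637. The third column assumes that 1000 patients have the measurement. The split proportions are assumptions. The Background's remark that close to half of patients remodel makes 50% plausible for remodelling, but not for LVEF, SVi, T1, T2 or ECV.

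**3. Illustrative power**

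Inputs: n = 1000 (the article's target is more than 1000), two-sided 0.05 (article), marker-outcome correlation 0.10 (assumed).

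- Linear: λ = atanh(0.10) × √997 = 0.1003 × 31.58 = 3.168. Power ≈ Φ(3.168 − 1.96) = 88.6%.
- 50% split: λ√0.637 = 2.528. Power ≈ Φ(0.568) = 71.5%.
- 20% split: λ√0.490 = 2.217. Power ≈ Φ(0.257) = 60.2%.

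A simulation of 600 replicates gave 88%, 68% and 62%. Its Monte Carlo standard error for the dichotomised results is about √(0.68 × 0.32/600) = 1.9 points, so the two approaches agree.

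A second check used two equal groups (500 each) that differ by an assumed 0.20 SD. Power is 88.5% for the continuous outcome, against 71.3%, 66.8% and 59.8% for splits of 50%, 30% and 20%. Over other assumed effects the range is:

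- 0.15 SD: 66.0% against 47.2% to 38.1%.
- 0.25 SD: 97.7% against 88.3% to 78.8%.

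With 500 patients, the first interim size, and 0.20 SD, it is 60.9% against 42.9% to 34.5%.

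**4. The hazard ratio**

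The sentence with the effect measures refers back to the models in the sentence before, which are logistic. Kaplan–Meier plots and the log-rank test, named for the secondary endpoint, are not regression models with covariate-specific hazard ratios. Nor can an odds ratio stand in for a hazard ratio. Under proportional hazards with a hazard ratio of 2.0, p₁ = 1 − (1 − p₀)². At p₀ = 0.30, p₁ = 0.51, and the odds ratio is (0.51/0.49)/(0.30/0.70) = 2.43. At p₀ = 0.10 it is 2.11, and at p₀ = 0.50 it is 3.00.

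**The case against.** The strongest defence is that the article is a condensed account. It speaks of predefined outcomes and of covariates, so thresholds and covariate lists may stand in a full protocol or analysis plan that is not shown. This is right as far as it goes. A reader might infer that the absent cut-points and covariates are errors, or that the cut-points will be chosen after seeing the data. The documents support neither. But predefined cut-points would not recover the lost information or produce a hazard ratio.

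A binary outcome may also be deliberate: the Background separates remodelers from non-remodelers, and the study aims at risk stratification. That justifies a yes/no remodelling analysis beside the continuous one. It does not justify logistic regression as the only model for T1, ECV or SVi. An ordinal logistic model would avoid a single cut, but the article names none, and it would give no hazard ratio either.

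The hazard ratio may be a misplaced term meant for the secondary endpoint. That is plausible, but the sentence ties it elsewhere and no hazard model is named, so it needs correcting.

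Two further stronger readings should be resisted:

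- **A wrong power claim.** The article makes none. Early CMR is done only in a subset, and echocardiography may replace CMR at 6 months, so figures per 1000 patients may not apply to T1, T2 and ECV.
- **A need to adjust for the index value.** Setting a linear model with a baseline covariate (98% power under an assumed correlation of 0.6) against an unadjusted logistic model (68%) mixes two changes, since the logistic model may also carry covariates. Index imaging follows the infarct and may lie on the path from metabolic state to outcome, so conditioning on it can remove part of the effect sought.

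**Conclusion.** The point holds as a mismatch in what the text fixes, not as a complaint about missing detail. One model is assigned to all primary endpoints, it suits only patency as defined, and one of its two stated effect measures cannot come from it.

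If the rule is followed, efficiency for a continuous endpoint drops to about 0.64 (50% split) or 0.49 (20% split) of a linear analysis. These factors assume a roughly normal outcome, a small effect and ordinary binary logistic regression. The power figures also rest on assumed effect sizes and full measurement, so they show the order of the loss and do not estimate this study's power.

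The cohort is exploratory and the measurements are recorded on their original scale. Nothing is lost if the text is corrected before analysis.

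**What to change.** In the Statistical approach section:

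1. Analyse the continuous 6-month endpoints (LVEF, SVi, increase in LVEDVi, T1, T2, ECV, and LV metabolism if it is retained as primary) by linear regression. Report mean differences or slopes with 95% confidence intervals.
2. Keep logistic regression with odds ratios for coronary patency.
3. Treat any yes/no remodelling threshold as a supportive analysis.
4. Remove the hazard ratio from the primary-endpoint models and attach it to a named Cox model for the 12-month secondary composite, beside the Kaplan–Meier plots and log-rank test.
5. If wanted, add adjustment for the index-hospitalisation value as a secondary or sensitivity analysis. State that it answers a different question in this observational cohort.

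The cost is a few sentences and no new data. Linear models require a check of residuals and, where needed, a transformation.

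### The 12-month secondary endpoint is assigned only an unadjusted log-rank test, which in this observational cohort can read age as a metabolic effect; the hazard ratio mentioned has no model that yields it

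*Protocol article*

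**What the plan says.** The Statistical approach section of the protocol article assigns methods endpoint by endpoint.

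- Primary endpoints: "For primary endpoints, logistic regression analysis will be used to model the predefined outcome data with impact of covariates". The next sentence reads "The effects of the independent parameters in these regression models will be estimated (odds ratio, hazard ratio", with 95% confidence intervals.
- Secondary endpoint: "Secondary endpoint analysis will be performed using Kaplan–Meier plots and the log-rank test". No covariate, stratification factor, Cox model or landmark is named for it.
- Significance: "Two-tailed p values below 0.05 will be considered indicative of statistically significant differences".
- Size: "No formal sample size calculation has been performed". The target is more than 1000 patients, with interim analyses after 500 and 1000.

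The design section describes an observational cohort. Its secondary composite combines death, MACCE and "rehospitalization due to heart failure within 12 months after STEMI", so the clock starts at the infarct. The stated objective is to find metabolic factors that drive outcome and could become therapeutic targets, which goes beyond describing prognosis. The Background says: "In elderly STEMI patients, metabolic comorbidities such as type 2 diabetes mellitus (T2DM), anemia, and chronic kidney disease (CKD) become increasingly prevalent". It also names rising age, multimorbidity and cardiogenic shock as offsetting gains in care.

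Exposures are measured at different times. Blood sampling and right heart catheterisation take place on day 0, the anaemia and iron work-up at V2 (day 1), and OGTT, spectroscopy and diabetes endotyping at V6: "Five days after pPCI (V6), we will again apply echocardiography and CMR with the addition of magnetic resonance spectroscopy (MRS").

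**The concern.** Groups defined by metabolic phenotype are not randomised. If the phenotype is commoner in older patients and older patients have more events, an unadjusted log-rank test rejects too often even when the phenotype has no effect at a given age. The article itself supplies both links for diabetes, anaemia and CKD. The test also cannot separate these overlapping conditions from one another, and it cannot use a continuous marker such as HOMA-IR or ferritin without cut-points. What is at stake is the main claim of the study: an older group could be reported as a metabolic risk phenotype.

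A second, narrower issue is timing. A patient who dies before V6 cannot be classified by OGTT, spectroscopy or endotype, yet the endpoint counts events from day 0.

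**Working it through.** The plan states no power, event count or calculated sample size, so there is no figure to reproduce. From the article come the two-sided 5% level, N of about 1000 (500 at the first interim), the 12-month window from the infarct, and the visit days. Assumed, because the article does not give them: exposed share p = 25–50%, 12-month event rate 10–20%, age gap 3–8 years, age hazard ratio h = 1.3–1.8 per 10 years, and age SD 12 years.

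**Age confounding.** Let the true age-conditional hazard ratio be 1, and let D be the number of events.

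- Apparent log hazard ratio: ln(h) × gap / 10.
- Expected test statistic: b = √(D·p·(1−p)) × apparent log hazard ratio.
- Rejection rate: Φ(b − 1.96) + Φ(−b − 1.96).

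Central case (p = 0.25, D = 150, gap 5 years, h = 1.5):
- apparent hazard ratio 1.5^0.5 = 1.22, with log 0.203
- b = √28.125 × 0.203 = 1.075
- rejection rate 0.188 + 0.001 = 18.9%

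Lowest case (p = 0.25, D = 100, gap 3, h = 1.3):
- apparent hazard ratio 1.08
- b = √18.75 × 0.0787 = 0.341
- rejection rate 6.3%

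Highest case (p = 0.5, D = 200, gap 8, h = 1.8):
- apparent hazard ratio 1.60
- b = √50 × 0.470 = 3.325
- rejection rate 91.4%

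Simulation with 2000 replicates per scenario (p = 0.25, event rate 15%) agrees with the approximation:

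| Scenario | Unadjusted log-rank | Age-stratified log-rank | Age-adjusted Cox |
|---|---|---|---|
| N 1000, no age gap | 5.8% | 5.7% | 5.6% |
| N 1000, gap 3, h 1.3 | 7.7% | 5.0% | 5.3% |
| N 1000, gap 5, h 1.5 | 19.8% | 5.0% | 4.6% |
| N 1000, gap 8, h 1.8 | 70.9% | 5.9% | 5.6% |
| N 500, gap 5, h 1.5 | 12.2% | 4.4% | 4.0% |

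**Timing.** The second simulation used N = 1000, half exposed, a null exposure, a true 12-month event rate of 15%, and an assumed 10%, 20% or 30% of those events in days 0–5.

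- All groups classified at day 5: the log-rank statistic is identical whether the clock starts on day 0 or day 5, and the null is rejected in 5.1–5.9% of studies. Only the event rate changes. With 10% early it is 0.15 × 0.9 / (1 − 0.015) = 13.7%, and with 20% and 30% early it is 12.4% and 11.0%, against a true 15%.
- One group known on day 0 (for example overt diabetes) and the comparator requiring the day-5 OGTT: the null exposure shows a hazard ratio of 1.12, 1.24 or 1.41, with false-positive rates of 9.9%, 24.1% or 49.7%.

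**The case against.** The best defence is the hazard ratio. A logistic model gives none and the secondary composite is the obvious time-to-event outcome, so a Cox model may be intended and simply unnamed in a condensed article. A reader might therefore infer that the plan rules out adjusted analysis. The article does not say that; it says what will be done and is silent on anything further. Even so, the wording ties the hazard ratio to the primary-endpoint models and names an unadjusted test for the secondary endpoint. The method is stated, and stated badly, so this is not just detail left to another document.

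Other points on that side stand in part.

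- The size is entirely assumption-driven and the lower end is trivial. The age link is stated for diabetes, anaemia and CKD, not for lipid exposures or data-driven clusters. The Background also reports higher 30-day mortality in patients without standard risk factors, a group growing particularly among the young. Age need not bias every comparison the same way.
- A reader might infer that starting the clock at the infarct invalidates every comparison. It does not. Day-0 samples and catheter measurements are unaffected, day-1 markers have only a short gap, and diabetes or CKD may exist before the infarct even if measured later. With all groups classified at V6, the test is unchanged.
- Adjusting for everything could harm. The article counts CKD among the metabolic comorbidities and links one diabetes endotype to kidney disease. Renal function and shock may be part of the exposure or lie on its path.
- Unadjusted curves by cluster are legitimate as prognostic description. The gap matters for claims about what drives outcome and about targets.

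**Conclusion.** The point holds in a limited form. For the secondary endpoint the article states an unadjusted test, in an observational cohort whose own Background gives reason to expect age confounding for three of the main exposures. The test can mislead, but the documents do not show that it will, or by how much. Under the assumed inputs the false-positive rate runs from about 6% to 91% and is about 19% in the central case. Age adjustment brings it to roughly 4–6% in every simulated scenario. The hazard-ratio wording is an error whichever model was meant.

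The timing issue is confined to exposures that need V6. It biases the test when groups are classified at different times or when early events decide who is measured. When all groups are classified at V6, it only lowers the reported event rate.

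**What to change.** - Make a Cox model for phenotype or continuous marker the main secondary analysis, adjusted for prespecified confounders that precede the exposure: at least age, sex and centre.
- Put renal function and cardiogenic shock in a separate, labelled model, because they may be part of the exposure or mediators.
- Keep Kaplan–Meier plots and the log-rank test as descriptive.
- Correct the text so that odds ratios belong to the logistic models and hazard ratios to the Cox model.
- Only for exposures that need V6 (OGTT, MRS, diabetes endotype), and above all where they are compared with groups known at admission, start follow-up at V6 for all groups and report earlier events separately.

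The cost is a change of analysis wording, with no new visit or measurement, and the Data Availability statement says the study is still recruiting. The downside is that early events leave the landmark analysis, so its results apply to patients who reach V6 free of the event.
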